**Figure 3 figure3:**
[figure not shown]
(A) Transcranial magnetic stimulation will be delivered over the primary motor area of the dominant hemisphere to find the optimal position for eliciting a motor evoked potential in the contralateral first dorsal interosseous muscle. (B) Intermittent theta burst stimulation parameters.

Participants will complete 3 maximal isometric contractions of the right FDI against an immovable structure. The duration of each contraction will be 5 seconds with a 30-second rest interval between trials. The largest EMG activity obtained from any of the 3 trials will be defined as the maximum voluntary contraction (MVC) of the FDI muscle for an individual. The level of EMG activity corresponding to 10% MVC will be displayed on an oscilloscope as a horizontal target line. Participants will be required to match the horizontal target line and maintain 10% MVC by contracting their right FDI during the acquisition of active motor threshold (AMT).

AMT will be defined as the lowest intensity required to evoke a MEP≥200 μV in 5 out of 10 consecutive trials while participants maintain approximately 10% MVC with their FDI [80,81]. This value will be determined using TMS_MTAT_2.0 freeware [82]. The stimulus intensity will be set to 37% maximum stimulator output, and 20 TMS pulses will be distributed over M1, specifically the FDI hot spot, with the stimulus intensity being adjusted after each subsequent pulse as advised by the MTAT software based on the presence or absence of an MEP on the previous trial [83]. Resting motor threshold (RMT) will be defined as the lowest intensity required to evoke a MEP≥50 μV in 5 out of 10 consecutive trials while participants maintaining the FDI at rest [80,81]. This value will be determined using TMS_MTAT_2.0 freeware.

To assess synaptic plasticity, an iTBS protocol (Figure 3B) will be delivered using biphasic pulses in bursts of 3 pulses delivered in 6 Hz trains that will last 2 seconds, followed by 8 seconds with no pulse delivered [50,84,85]. iTBS will be repeated for a total of 612 pulses at 80% of AMT [86]. To assess synaptic plasticity 20 MEPs will be delivered at 120% of RMT. The average of 20 MEPs will be recorded from FDI before and immediately following iTBS.

#### Cognitive Function

Cognitive functions will be assessed using the National Alzheimer’s Coordinating Center Uniform Data Set Neuropsychological Battery, Version 3, comprised of the Montreal Cognitive Assessment, Semantic and Verbal Fluency, Trail-making Tests, Digit Span, Benson Complex Figure Test, and the Multilingual Naming Task.

#### Brain Derived Neurotropic Factor and Osteocalcin

Blood will be collected after ≥10-hour fast from an antecubital vein at T0 and T1 in red top BD Vacutainer collection tubes (Becton, Dickinson and Company, Franklin Lakes, NJ, USA). Red top tubes will be left to clot at room temperature for 45 minutes and subsequently centrifuged at 3488×g for 10 minutes at 4°C. Serum will be aliquoted into vials and stored at –80°C. Enzyme-linked immunosorbent assay (ELISA) assays will be carried out for the determination of serum BDNF (R&D Systems, Inc, Minneapolis, MN, USA) and total OCN (Human Osteocalcin ELISA kit KAQ1381). After incubation with 5 mg/ml hydroxylapatite (Invitrogen-Thermo Fisher Scientific, Carlsbad, CA, USA) to remove carboxylated OCN [87], serum uncarboxylated OCN will be measured by ELISA. Carboxylated OCN will be determined by subtracting uncarboxylated OCN from the total OCN [74].

#### Participant Experience

A Likert-type scale (0-4) will be given to participants to rate their enjoyment of the self-determined intensity interval training intervention (exercise group) and the overall research experience during the last visit (exercise and no exercise group).

#### Compliance

We will quantify the number of participants who demonstrate compliance with the exercise schedule. An individual is deemed 100% compliant if they attend all exercise sessions (3 times per week × 4 weeks=12 sessions). Attendance lower than this will be quantified as a percentage of the total number of sessions (out of 12).

### Data Exclusion

Peak-to-peak amplitudes of the MEPs will be collected by the experimenter. Trials will be examined visually, and any trials presenting with EMG activity prior to TMS stimulus artifact will be discarded from the analysis. The remaining EMG data will be analyzed using Signal Software (Cambridge Electronic Design).

### Statistical Analysis Plan

To investigate the difference in the magnitude of synaptic plasticity between groups, an unpaired *t* test will compare the percentage change in synaptic plasticity (from T0 to T1) between the 2 groups (exercise and no exercise). Similarly, the effect of exercise on serum BDNF and OCN levels will be assessed using an unpaired *t* test comparing the change in levels from T0 to T1. Significance will be set to =.05.

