**Methods:**

24 individuals diagnosed with MCI will be recruited for assignment to 1 of the 2 equally sized groups: exercise and no exercise. The exercise group will perform exercise 3 times per week for 4 weeks. Synaptic plasticity will be measured before and following the 4-week intervention. At these time points, synaptic plasticity will be measured as the response to single-pulse TMS, reflected as the percent change in the average amplitude of 20 motor-evoked potentials before and after an iTBS rTMS protocol, which is used to induce synaptic plasticity. In addition, individuals will complete a battery of cognitive assessments and provide a blood sample from the antecubital vein to determine serum brain-derived neurotrophic factor and osteocalcin.

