In humans, synaptic plasticity, and more specifically, LTP-like effects can be assessed in vivo by delivery of transcranial magnetic stimulation (TMS) in protocols called intermittent theta burst stimulation (iTBS) and 5-Hz repetitive TMS (5-Hz rTMS). Both forms delivered over the motor cortex induce LTP-like effects as measured by short-term increases in the efficacy of the corticospinal pathway from cortex to muscle [50,51]. These effects are analogous to animal models of LTP since they are mediated by glutamate and require glutamate binding at *N*-methyl-D-aspartate (NMDA) receptors [51]. In humans, the decline in neuronal excitability and synaptic function seen with aging contributes to memory loss as well as sensory and motor deficits [52]. Thus, in humans, iTBS and 5-Hz rTMS are noninvasive tools to assess whether aging and MCI populations demonstrate synaptic plasticity and whether interventions such as exercise can enhance the magnitude of synaptic plasticity. Compared to age-matched controls, individuals with MCI demonstrate blunted synaptic plasticity as indicated by a reduced response to 5-Hz rTMS [53] and iTBS [54]. These effects are reflected as decreases in motor evoked potentials (MEP) when compared to healthy controls. Healthy controls demonstrate MEP facilitation, as expected, observed by an increase in MEP amplitude during the delivery of a 5-Hz train. In contrast, 5 Hz–induced MEP facilitation is not seen in individuals with MCI, suggesting deficits of glutamate pathways responsible for synaptic potentiation [53]. The delivery of iTBS has yielded similar results in patients with MCI, demonstrating a lack of MEP facilitation [54].

Brain-derived neurotrophic factor (BDNF) is a key regulator of processes crucial for cognition, particularly learning and memory [55-57]. The presynaptic release of BDNF influences the activation, trafficking, and expression of NMDA receptors as a result of enhanced calcium influx. This calcium influx is thought to allow for the release of BDNF at the postsynaptic terminal. Postsynaptic BDNF release is essential for presynaptic vesicle cycling, which increases synaptic plasticity, ultimately leading to improvements in cognitive functioning [58]. BDNF expression is correlated with cognitive function [57] and is consistently elevated following exercise in healthy older adults, suggesting that the rise in BDNF levels with long-term exercise may reduce mental deterioration in patients with MCI [55].

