### Power

This pilot study will recruit 24 participants aged 55-80 years old diagnosed with MCI. To determine this sample size, the following features were included in an a priori calculation using G*Power (Heinrich-Heine-Universität Düsseldorf), α=.05, Power (1-β)=0.9, and the effect size was calculated using Trebbastoni et al’s findings [53].

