### Experimental Design

Individuals will be recruited for assignment to 1 of the 2 equally sized groups: exercise or no exercise. The exercise group will perform the exercise intervention. The no exercise group will serve as the control.

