## Discussion

### Overview

This pilot project is the first to assess changes in synaptic plasticity following a 4-week, self-determined, interval exercise training in individuals with MCI. Individuals will be assigned to 1 of the 2 groups (exercise or no exercise). The exercise group will participate in 12 sessions of exercise across 4 weeks (3 sessions per week). The no exercise group will not participate in the exercise regime, instead, they will be asked to return 4 weeks after their initial visit. Measures of synaptic plasticity, cognition, BDNF, and OCN will be assessed at baseline and 4 weeks later.

Previous research has demonstrated the positive benefits of exercise in individuals diagnosed with MCI. The 12 weeks of resistance training in individuals with MCI improved attention and working memory, and elicited changes in EEG activity [30]. In addition, 2 days of aerobic exercise in MCI subjects improved memory recall [26]. The 12 weeks of aerobic exercise in subjects with MCI improved cognition as reflected by changes in the Mini Mental State Exam [34]. These findings provide evidence that aerobic exercise is capable of modifying cognition in individuals with MCI. It remains unknown whether these improvements in cognition are a result of increases in synaptic plasticity following aerobic exercise.

Our study aims to determine whether synaptic plasticity is modified following 4 weeks of self-determined interval exercise training. Further, we will determine whether any changes in synaptic plasticity correlate with changes in cognition, BDNF, or OCN levels. We anticipate that the exercise group will demonstrate an increase in synaptic plasticity after 4 weeks of exercise compared to the no exercise group. If synaptic plasticity increases in the exercise group, this will be interpreted as a mechanism by which exercise improves cognition in MCI. Further, we hypothesize a positive relationship between a change in synaptic plasticity and measures of serum BDNF and OCN.

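### Read as written, the main test divides by baseline plasticity, itself a signed percent change that the protocol expects to be near zero in MCI

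*Protocol article*

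**What the plan says.** Three statements in the protocol article combine.

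- **Visit-level measure.** The abstract (Methods) says synaptic plasticity at each time point is "reflected as the percent change in the average amplitude of 20 motor-evoked potentials before and after an iTBS rTMS protocol". The Synaptic Plasticity section, after Figure 3, describes the matching recording: "The average of 20 MEPs will be recorded from FDI before and immediately following iTBS".
- **Main test.** The Statistical Analysis Plan section specifies an unpaired t test that "will compare the percentage change in synaptic plasticity (from T0 to T1) between the 2 groups (exercise and no exercise"). For serum BDNF and osteocalcin, the next sentence words the contrast differently: "comparing the change in levels from T0 to T1".
- **Expected baseline.** The Introduction says of MCI: "The delivery of iTBS has yielded similar results in patients with MCI, demonstrating a lack of MEP facilitation".

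The Discussion (Overview) gives the expected direction: "We anticipate that the exercise group will demonstrate an increase in synaptic plasticity after 4 weeks of exercise compared to the no exercise group". The article gives no other formula for the T0–T1 contrast and no rule for zero or negative baseline values.

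**The concern.** The visit-level measure is already a percent change, so it can be positive, zero or negative. Taking a further percentage change from T0 to T1 puts that signed value in the denominator. The trial's own rationale is that people with MCI fail to facilitate after iTBS, which places the denominator close to zero.

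A ratio with such a denominator does not rank participants by benefit. Improvement from a negative baseline counts against exercise, and a trivial positive baseline can yield a score of many hundreds of percent. With 12 participants per arm, one or two such values can dominate the mean and variance in the t test. This is the test for Aim 1. If the same score were carried into the Aim 2 correlations with BDNF, osteocalcin and cognition, they would inherit the problem.

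**Working it through.** **1. The plan's own figure.** The Power section says: "This pilot study will recruit 24 participants aged 55-80 years old diagnosed with MCI", with α = .05 and power 0.9. The Experimental Design section describes "assignment to 1 of the 2 equally sized groups: exercise or no exercise", hence 24/2 = 12 per arm. The article prints neither the effect size nor the sidedness, so N = 24 can be neither confirmed nor refuted. Back-solving an unpaired t test at 12 per arm with the noncentral t distribution gives a standardised difference of 1.385 (two-sided) or 1.233 (one-sided). The two-sided value sets the benchmark below.

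**2. Arithmetic of the three possible scores.** Let T0 and T1 be the percent MEP change across iTBS at each visit.

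- Literal: 100 × (T1 − T0)/T0
- Difference: T1 − T0, in percentage points
- Ratio: 100 × (R1 − R0)/R0, where R = 1 + T/100 is the post/pre ratio

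| T0 → T1 | Literal | Difference | Ratio |
|---|---|---|---|
| +2% → +20% | 100 × 18/2 = +900% | +18 | 100 × 0.18/1.02 = +17.6% |
| −10% → +20% | 100 × 30/(−10) = −300% | +30 | 100 × 0.30/0.90 = +33.3% |
| −10% → −20% | 100 × (−10)/(−10) = +100% | −10 | 100 × (−0.10)/0.90 = −11.1% |
| 0% → +20% | undefined | +20 | +20% |

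Under the literal score, the participant with the largest gain in points scores lowest, and the one who worsens scores above zero.

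**3. Simulation on the log-ratio scale.** Settings: 20,000 trials each, 12 per arm, two-sided 0.05, T0 and T1 log post/pre ratios bivariate normal. Assumed, not in the documents: log mean 0, 0.1 or 0.2 (e^0.1 − 1 ≈ +10%, e^0.2 − 1 ≈ +22%), SD 0.2–0.5, T0–T1 correlation 0.3–0.5. The exercise shift is 1.385 SD of the change, so a t test on the change in log ratio has 90% power by construction.

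- Literal score, log mean 0: about 1% significant in the right direction and about 1% in the wrong direction. The estimate has the right sign about half the time.
- Literal score, log mean 0.1 to 0.2: about 2–9% in the right direction.
- Percentage-point difference, same data: about 91–93%.
- Percentage change of the ratio, same data: about 84–90%.

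**4. Simulation on the percentage-point scale, with a wider range of baselines.** Same design, but T0 and T1 are normal in percentage points, with SD 20–40 and correlation 0.3–0.6 (assumed). The shift is set so that the simple difference has 90% power.

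| Mean T0 | Share with T0 < 0 | Literal score: right direction | Literal score: wrong direction |
|---|---|---|---|
| −10% | 60–69% | below 1% | 2–4% |
| 0% | 50% | about 1% | about 1% |
| +10% | 31–40% | 2–3% | below 1% |
| +20% | 16–31% | 3–8% | below 1% |
| +50% | 1–11% | 11–50% | 0% |
| +100% | 0–1% | 45–82% | 0% |

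At mean T0 of 0%, about 53% of exercise participants who truly improve receive a negative score. The median largest absolute score in a trial is about 2,700–3,500%.

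**The case against.** The strongest reply is that one condensed sentence is being read too literally. Because the visit-level measure is itself called a percent change, the analysis wording may simply name that measure, with T0 to T1 identifying the contrast. The score is then a difference in percentage points and the problem disappears. Alternatively, the Synaptic Plasticity section only records mean MEPs before and after iTBS. If plasticity is held as a post/pre ratio, its percentage change has a positive denominator and never flips sign. Both readings are possible and the planned t test works under each. Against them, the abstract does say percent change, and the adjacent sentence uses a plain change for BDNF and osteocalcin. The literal reading is the more natural one, though not the only one.

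A reader might also infer that many participants will have negative baselines, or that the trial cannot detect its effect. The documents do not support either as a flat statement. The Introduction reports a lack of facilitation at group level, and also describes a blunted or reduced response. It gives no mean, SD or share of negative responders. The 50% negative share follows from assuming a mean of zero. The 90% benchmark is likewise constructed, so the power figures contrast endpoints and do not estimate this trial's power.

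Finally, this is an article about a pilot study, and a fuller document may hold the formula. That matters less, because the point is not an omission: the section states the variable and the test, and what it states misbehaves if followed.

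**Conclusion.** The point holds in conditional form. Taken literally with the abstract's definition, the main endpoint is undefined at zero, reverses direction for negative baselines and is very heavy-tailed. These properties are plain arithmetic and need no assumption about the data.

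The size of the power loss does depend on assumptions. Against a 90% benchmark at 12 per arm, the literal score has about 1% right-direction power if mean T0 is near 0%, and about 2–9% at about +10% to +22%. The loss is partial at +50% to +100%, although the Introduction makes such baselines unlikely in this population. Under the percentage-point or ratio reading, power is about 84–93% in the log-ratio settings and there is no defect beyond unclear wording. It would be wrong to conclude that the trial is bound to miss a real effect, because that requires both the literal reading and a baseline near zero relative to its spread. Confidence is moderate, since it rests on how one sentence is read.

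**What to change.** Replace the phrase in the Statistical Analysis Plan section with an explicit formula: the contrast is T1 minus T0 in the visit-level iTBS response, in percentage points, and T0 plasticity is never used as a divisor. That alone cures the defect.

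Preferably, define plasticity at each visit as the log of mean MEP after iTBS over mean MEP before iTBS. Analyse the T1 log ratio by ANCOVA with group and the T0 log ratio as covariate, and report the group difference, back-transformed to a ratio, with a 95% CI. This is a preference for precision and is not needed to remove the problem.

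Use the same scale for the sample-size calculation and for the Aim 2 correlations. If a fuller protocol already gives one of the workable formulas, align the article's wording with it. The cost is one sentence and, for ANCOVA, one degree of freedom. No new data are needed.

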### Experimental Protocol

The dependent measures of synaptic plasticity, cognition, and venous blood BDNF and OCN, will be measured before and after the 4-week intervention (Figure 1).

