### Conclusions

The data obtained from this research study will provide valuable insights into the compliance of a self-determined intensity interval exercise in the MCI population. Exercise provides an affordable and accessible opportunity to promote changes in cognition. This study will determine whether exercise alters synaptic plasticity in a population with impaired cognition.

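### The stated analysis has between-arm tests for plasticity, BDNF and OCN but none for cognition, yet a plasticity gain is to be read as explaining a cognitive benefit of exercise

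*Protocol article*

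**What the plan says.** The Experimental Protocol section treats cognition on a par with the other outcomes: "The dependent measures of synaptic plasticity, cognition, and venous blood BDNF and OCN, will be measured before and after the 4-week intervention". The Figure 1 legend and the Discussion (Overview) confirm that all participants, controls included, are measured at T0 and T1.

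The Statistical Analysis Plan section gives an unpaired t test between arms for percentage change in plasticity. It then says that "the effect of exercise on serum BDNF and OCN levels will be assessed using an unpaired" t test on change. Cognition is not mentioned there.

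Cognition has an analytic role only in Aim 2, restated in the Overview: "we will determine whether any changes in synaptic plasticity correlate with changes in cognition, BDNF, or OCN levels". The same paragraph also sets an interpretation rule. If plasticity rises in the exercise group, the rise will be taken as a mechanism for the cognitive benefit of exercise in MCI. The rule has no condition on the cognition data.

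**The concern.** The rule joins two claims: that exercise raised plasticity, and that exercise benefits cognition with plasticity as the route. The stated tests address only the first. Cognition in the exercise arm could be no better than in controls, or worse, and the stated reading would still apply.

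The correlation looks as if it might supply the missing evidence, but it answers another question: whether people whose plasticity rose more also gained more on the battery. That can be true when exercise does nothing for cognition, and false when exercise helps everyone equally.

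The battery is also repeated after only 4 weeks, so gains from retesting are plausible (the article gives no figure). Comparison with the control arm would remove them, and those data are already being collected.

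**Working it through.** **1. Measures against stated analyses**

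| Measure | Both arms, T0 and T1 | Between-arm test stated | Other stated use |
|---|---|---|---|
| Plasticity | yes | unpaired t test | Aim 2 |
| BDNF | yes | unpaired t test | Aim 2 |
| OCN | yes | unpaired t test | Aim 2 |
| Cognition | yes | none | Aim 2 |

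**2. Inputs**

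- Size: "This pilot study will recruit 24 participants aged 55-80 years old diagnosed with MCI" (Power). Allocation: "Individuals will be recruited for assignment to 1 of the 2 equally sized groups: exercise or no exercise" (Experimental Design). Hence 24/2 = 12 per arm.
- Design: "α=.05, Power (1-β)=0.9, and the effect size was calculated using" a cited study (Power). The effect size itself is not given, so the total of 24 cannot be reproduced. It can only be solved backwards.
- Back-solved effect: for an unpaired t test with n = 12 per arm, df = 22 and noncentrality d·√(n/2) = d·√6. Power of 0.90 needs d = 1.385 two-sided (1.385 × 2.449 = 3.39), or d = 1.233 one-sided. I use 1.385 below as an assumed plasticity effect.

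**3. How often the rule would fire with no cognitive effect**

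The rule depends on plasticity alone. If a rise means a significant plasticity t test and the true effect is d = 1.385, it fires in about 90% of trials by construction, whatever happens to cognition.

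**4. Can the correlation stand in for an arm comparison?**

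Model, in SD units of change, with g = 1 for exercise and 0 for control:

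- plasticity change = d_p·g + e
- cognition change = d_c·g + r·e + √(1 − r²)·u, with e and u independent standard normal.

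Two-sided 0.05, 12 per arm, at least 20,000 simulated trials per row. The article does not say whether the correlation is adjusted for arm, so both forms are shown (adjusted: 21 df; pooled: 22 df, with d_p = 1.385).

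| Truth (assumed) | Correlation, arm-adjusted | Correlation, pooled | Arm t test on cognition change |
|---|---|---|---|
| No cognitive effect, r = 0.6 | 89% | 70% | 5% |
| No cognitive effect, r = 0.5 | 71% | 52% | 5% |
| Cognitive effect 1 SD for everyone, r = 0 | 5% | 23% | 65% |

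The pooled figure is lower in the first two rows because the arm difference in plasticity adds variance unrelated to cognition. The expected pooled correlation is about r/√(1 + d_p²/4) = 0.6/√(1 + 0.480) = 0.49. It is higher in the last row because two arm effects alone create a pooled correlation of about (d_p·d_c/4)/√[(1 + d_p²/4)(1 + d_c²/4)] = 0.346/√(1.480 × 1.25) = 0.25. In either form, significance does not track whether exercise changed cognition.

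**5. What an arm comparison would deliver**

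- ANCOVA of the T1 score on arm and T0 score: SE = √[(1 − ρ²)·2/12] in SDs of the score, with t(21) = 2.08.
 - ρ = 0.7: √(0.51/6) = 0.292; half-width 2.08 × 0.292 = 0.61 SD.
 - ρ = 0.8: √(0.36/6) = 0.245; half-width 2.08 × 0.245 = 0.51 SD.
- t test on change: half-width t(22)·√(2/12) = 2.074 × 0.408 = 0.85 SD of the change score. Multiplying by √[2(1 − ρ)] converts this to SDs of the score: 0.66 (ρ = 0.7) or 0.54 (ρ = 0.8), slightly wider than ANCOVA.
- Power of the change-score t test: 11% at d = 0.3, 22% at 0.5, 47% at 0.8, 65% at 1.0 (change-score SDs).

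**The case against.** The strongest reply is that this is a condensed article. Its analysis section is three sentences long and also gives no method for the Aim 2 correlation or for compliance, so it is visibly not a full list. A reader might infer that the trial will never estimate the effect of exercise on cognition. The article does not support that, since a fuller analysis plan may contain the contrast. What stands is narrower: the article states no such contrast, and it does state an interpretation that needs one.

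Second, no aim or hypothesis concerns an arm difference in cognition. The aims are plasticity, its correlates and compliance, and the article never claims that the correlation estimates an arm effect. It rests the exercise–cognition link on earlier studies. This is fair, and it is why the contrast belongs in an exploratory tier. It does not rescue the rule. The Introduction concedes that some exercise studies found no cognitive improvement, so a benefit from this particular 4-week regimen cannot be taken as given.

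Third, a reader might infer that the trial's conclusions are themselves about cognition, from the line "Exercise provides an affordable and accessible opportunity to promote changes in cognition". That line is general background. The Conclusions section states the study's own question as plasticity, with compliance beside it. Nor does the limitations paragraph plan a larger trial on the strength of a cognitive effect: it names compliance and the exercise regime.

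Finally, 12 per arm gives little power for a modest cognitive effect. That is true, and it is a reason to report an interval rather than a verdict.

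**Conclusion.** The point holds in limited form. The article states a between-arm test for three of its four dependent measures and none for cognition, and it fixes a reading of the plasticity result that presupposes a cognitive benefit. As written, that reading can be reached with no cognitive difference from control, and the Aim 2 correlation would not reveal the error.

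The percentages rest on assumed within-arm correlations, an assumed 1 SD cognitive effect, and a plasticity effect inferred from the sample size rather than stated. They shift with those choices and with arm adjustment (89% against 70% in the main case). The direction does not. The plasticity comparison itself is unaffected.

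**What to change.** Add to the Statistical Analysis Plan section, for example: *As an exploratory analysis, one prespecified cognitive score at T1 will be compared between arms by ANCOVA with its T0 value as covariate, and the difference reported with a 95% CI.* Name the score before any data are analysed. One option is the mean of the battery's test z-scores, each standardised to its T0 mean and SD, with timed tests reversed. Use the same score in the Aim 2 correlation, which also prevents selection among the battery's tests after the fact.

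Then amend the Discussion (Overview): either make the mechanism reading conditional on the cognitive contrast, or limit it to a statement that exercise changed plasticity. If a fuller plan already contains the contrast, citing it and amending this sentence is enough.

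The cost is a few sentences and one extra model, with no new data. The drawback is a wide interval, about ±0.5 to ±0.6 SD under the assumed T0–T1 correlations of 0.8 to 0.7. It must be reported as exploratory, and a null result must not be read as absence of effect.

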**Figure 1 figure1:**
[figure not shown]
Dependent measures will be obtained in all participants 2-3 days before (T0) and following the exercise intervention (T1). Synaptic plasticity assessed using transcranial magnetic stimulation, cognitive function assessed by neuropsychological battery, and blood draws for serum BDNF and osteocalcin will be performed before and immediately following the intervention. BDNF: brain-derived neurotrophic factor; OCN: osteocalcin; rTMS: repetitive transcranial magnetic stimulation.

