A limitation of this study is the use of self-determined interval training, whereby participants determine their own level of exertion. Individuals living with MCI will have varying physical and cognitive abilities which may limit their capacity to perform exercise at an imposed intensity. However, previous research has shown that only individuals who increase their fitness over the exercise period exhibit increased serum BDNF levels [88]. We hope that our approach of tailoring the exercise to the individual will increase the feasibility and retention of the study, thus creating a realistic and effective exercise regimen for individuals with MCI. A second limitation is that we do not consider biological sex or gender in the randomization due to the small sample size. If the study is successful in providing data to support compliance and the exercise regime, it will inform a larger-scale study of exercise training in MCI with biological sex and gender included.

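### BDNF and osteocalcin are compared on raw change scores; adjusting the T1 level for T0 by ANCOVA would be at least as precise unless the T0–T1 correlation is about 0.9 or higher

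*Protocol article*

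**What the plan says.** Under Statistical Analysis Plan, the protocol article names a two-sample *t* test for each serum marker. It describes that test as "comparing the change in levels from T0 to T1". No baseline covariate is named. The section closes with "Significance will be set to =.05".

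The baseline values needed for an adjusted analysis will be in hand. The section on BDNF and osteocalcin says "Blood will be collected after ≥10-hour fast from an antecubital vein at T0 and T1", and the Figure 1 caption says the dependent measures are taken at both time points in every participant.

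The Abstract gives the size: "24 individuals diagnosed with MCI will be recruited for assignment to 1 of the 2 equally sized groups", so 12 per arm. The limitations part of the Discussion says "we do not consider biological sex or gender in the randomization due to the small sample size", which implies that allocation is random.

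**The concern.** A test on T1 minus T0 subtracts the whole of each participant's baseline. That is the right amount only if a difference of one unit at T0 predicts a difference of one unit at T1. With equal SDs at the two visits the predictive slope is ρ, and for any ρ below 1 the subtraction takes away too much. An arm that happens to start low then appears to rise, and one that starts high appears to fall.

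Two things are at stake for the serum markers: intervals that may be wider than the data require, and an estimate that in any one trial moves against the baseline imbalance seen. Both matter more with 12 per arm than in a large trial. The markers are secondary, but they carry part of the mechanistic argument in aim 2 and in the Discussion.

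**Working it through.** **Plan's own figure.** The Power section gives "α=.05, Power (1-β)=0.9, and the effect size was calculated using" a cited study, and a total of 24. No numerical effect size is printed, so 24 cannot be reproduced. Solving backwards with the noncentral *t*, 12 per arm at 90% power needs a standardized difference of about 1.39 (two-sided) or 1.23 (one-sided). Nothing below depends on this.

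**Inputs from the article.** 12 per arm; T0 and T1 values in all participants; unpaired *t* test on the change.

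**Assumptions.** Equal SD σ at T0 and T1, and random allocation. The correlation ρ is not given, so a range is shown.

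**Baseline imbalance.** Let D be the exercise-minus-control difference at T0, in SD units.

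- SE(D) = √(2/12) = 0.41.
- P(|D| > 0.5) = 2[1 − Φ(0.5/0.408)] ≈ 0.22.
- Given D, the change-score estimate is off by −(1−ρ)D. The average over D is zero.

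**Precision.**

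- Change score: variance per person 2σ²(1−ρ).
- ANCOVA: residual variance σ²(1−ρ²).
- Ratio: (1−ρ²)/[2(1−ρ)] = (1+ρ)/2.
- Allowance for estimating the slope at N=24: 1 + 1/(24−4) = 1.05.
- Break-even: 1.05(1+ρ)/2 = 1, so ρ = 2/1.05 − 1 ≈ 0.90.

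The simulated column comes from 60,000 trials per ρ with 12 per arm. The power column is simulated ANCOVA power where the true effect gives the change-score test 80%. The last column is −(1−ρ)D at D = +0.41.

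| ρ | (1+ρ)/2 | × 1.05 | Simulated ratio | ANCOVA power | Shift in change-score estimate (SD) |
|---|---|---|---|---|---|
| 0.3 | 0.650 | 0.6825 | 0.688 | 92% | −0.29 |
| 0.5 | 0.750 | 0.7875 | 0.786 | 88% | −0.20 |
| 0.7 | 0.850 | 0.8925 | 0.894 | 84% | −0.12 |
| 0.8 | 0.900 | 0.9450 | 0.943 | 82% | −0.08 |
| 0.9 | 0.950 | 0.9975 | 0.995 | 80% | −0.04 |
| 0.95 | 0.975 | 1.0238 | 1.026 | 79% | −0.02 |

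In the simulation, the ANCOVA estimate showed essentially no dependence on D (slopes between −0.002 and 0.008), while the change-score estimate followed −(1−ρ).

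Below ρ = 0.5 the change score is noisier than comparing T1 alone, because 2(1−ρ) is then greater than 1.

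**The case against.** The strongest reply is that nothing here is an error. With random allocation the change-score *t* test is a legitimate analysis, unbiased over repeated trials. Change is also the quantity that aim 2 correlates with change in plasticity. The gain depends on a correlation the article does not give. The samples are fasting and only about four weeks apart, so a high ρ cannot be excluded, and at 0.9 or above there is nothing to gain. All of this stands, and it limits the point to efficiency and conditional error in secondary markers of a pilot.

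The equal-SD assumption affects the size more than the direction. With SDs σ₀ at T0 and σ₁ at T1, the change-score variance minus the ANCOVA variance, before the slope allowance, is (σ₀² + σ₁² − 2ρσ₀σ₁) − σ₁²(1−ρ²) = (σ₀ − ρσ₁)². This is never negative.

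The preference for ANCOVA also needs random allocation. The article mostly speaks of assignment and mentions randomization only among its limitations. If allocation were not random, the two analyses could answer different questions.

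A reader might infer more than the article supports:

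- That chance imbalance is left uncorrected. It is not: T0 is subtracted in full, and the leftover error has the opposite sign to the imbalance.
- That a large imbalance is to be expected. One above 0.5 SD has only about a 22% chance.
- That the trial is underpowered for these markers. No power is claimed for them, and the 80% reference in the table is only illustrative.
- That cognition has the same fault. The section states no between-group test for the cognitive scores.

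**Conclusion.** The point holds as a modest weakness in the analysis. The stated test is valid under randomization, but it over-corrects chance baseline differences, and unless ρ reaches about 0.9 it gives up precision that data already being collected could supply. With equal SDs, the variance saved at N=24 is about 32% at ρ = 0.3, 21% at 0.5, 11% at 0.7, 6% at 0.8 and nil at 0.9; at 0.95 ANCOVA costs about 2%. With ρ unknown, that asymmetry favours prespecifying ANCOVA.

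The conclusion rests on random allocation, the equal-SD assumption for the exact sizes, and an assumed range for ρ. It does not show the planned test to be biased or invalid.

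**What to change.** In the Statistical Analysis Plan, replace the change-score *t* tests for the serum markers with this: the T1 level of BDNF, and of each OCN measure analysed, will be compared between groups by ANCOVA with the T0 level of the same measure as covariate, and the adjusted group difference (or ratio, if analysed on the log scale) will be reported with its 95% CI.

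Use the log scale only where the values are positive and skewed. The article gives no distributions, and carboxylated OCN is obtained by subtracting one assay result from another, so values near or below zero cannot be ruled out. The variance ratios above compare both methods on one common scale and do not measure any gain from transforming.

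Change scores can be kept for the aim 2 correlations. It would help to say plainly in Experimental Design that assignment is random, because the adjusted comparison relies on it.

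The cost is one sentence of text and one degree of freedom (21 instead of 22). Visits, assays and sample size do not change.
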